## Abstract

**Background:**

Oocyte aneuploidy is a major cause of pregnancy failure in women of advanced maternal age (AMA), and current assisted reproductive technologies offer limited effective strategies to prevent age-related decline in oocyte quality. The mevalonate (MVA) pathway in granulosa cells has recently been implicated in supporting meiotic maturation, but its therapeutic potential in humans remains unclear. This randomized controlled trial is designed to evaluate the effects of MVA supplementation on oocyte competence in women of AMA undergoing preimplantation genetic testing for aneuploidy (PGT-A).

**Methods:**

The study will be conducted as a single-center, prospective, randomized controlled trial. A total of 128 infertile women aged 38–42 years undergoing PGT-A will be enrolled and randomized to either the MVA supplementation group or the control group. Cumulus-oocyte complexes retrieved from each cycle will be allocated according to the randomization protocol, with an estimated 150 cycles analyzed. The primary outcome is the euploidy blastocyst rate, while the secondary outcomes are the clinical pregnancy rate and live birth rate following frozen embryo transfer (FET).

**Discussion:**

This trial is expected to evaluate the effects of MVA supplementation on euploidy blastocyst rate and clinical pregnancy outcomes in women of AMA undergoing PGT-A. These findings may provide valuable insights into the potential application of MVA supplementation as an adjunct treatment for infertility in this population.

**Trial registration:**

ClinicalTrials.gov NCT05788822. Registered in March 2023.

## Administrative information

Note: The numbers in curly brackets in this protocol refer to SPIRIT checklist item numbers. The order of the items has been modified to group similar items (see http://www.equator-network.org/reporting-guidelines/spirit-2013-statement-defining-standard-protocol-items-for-clinical-trials/).

## Introduction

### Background and rationale {6a}

Oocyte aneuploidy is a major contributor to age-related fertility decline and a principal cause of pregnancy loss. Over the past decades, a global shift in reproductive behavior—most notably delayed childbearing—have increased the proportion of conceptions in older women and the incidence of age-associated fertility challenges [1]. Multiple factors contribute to these difficulties, among which declining oocyte quality—characterized by meiotic chromosome segregation errors—is a leading determinant and increases the risk of aneuploidy [2]. Epidemiological and clinical studies consistently show that the prevalence of aneuploid metaphase II oocytes rises sharply after the mid-30 s, with rates more than doubling in women beyond 34 years of age [3, 4]. Although postfertilization mitotic errors also contribute to chromosomal abnormalities, current evidence strongly supports that maternal age-related meiotic disturbances constitute the predominant origin of embryo aneuploidy [3, 5].

Proposed interventions to delay ovarian aging such as intraovarian stem-cell or platelet-rich plasma procedures remain investigational, and none has yet been proven in clinical trials to preserve oocyte genomic stability with advancing age [5, 6]. Assisted reproductive technologies (ART) including genetic testing for aneuploidy (PGT-A) permit selection of euploid embryos and inform transfer strategies but do not reduce the initial high frequency of aneuploid embryos seen in AMA. Current clinical guidelines advise PGT-A and frozen single embryo transfers for women with age-related fertility concerns [7]. However, embryo usability declines sharply after age 43 following PGT-A, underscoring the need for upstream biological interventions to improve oocyte quality at its source.

Emerging evidence implicates the mevalonate (MVA) pathway—a central metabolic route in cholesterol biosynthesis—in the regulation of meiotic maturation and genomic stability. As the primary regulator of cholesterol homeostasis, which undergoes age-related alterations [8], the MVA pathway supports oocyte maturation partly through luteinizing hormone receptor (LHR) and epidermal growth factor (EGR) signaling. Our prior investigations identified a marked suppression of MVA-related gene activity in granulosa cells from AMA patients compared to younger counterparts [8]. In animal models, exogenous MVA compounds have shown promise in correcting meiotic abnormalities and reducing aneuploidy rates in aging oocytes [8]. However, despite these mechanistic insights and preclinical data, the effect of MVA supplementation on euploid blastocyst formation in women of AMA remains unknown.

Given the potential role of MVA in restoring oocyte quality and the lack of effective interventions for women of AMA, this study proposes a randomized controlled trial to evaluate MVA supplementation during the pre-fertilization phase in women aged 38–42 undergoing PGT-A cycles, thereby facilitating clinical translation and potential integration into ART practice.

### Objectives {7}

To evaluate whether brief MVA supplementation in vitro prior to fertilization increases the yield of euploid embryos in women of AMA.

### Trial design {8}

This is a single-center, prospective, randomized, within-subject controlled superiority trial with a theoretical 1:1 allocation of cumulus-oocyte complexes (COCs) to intervention vs. control.

## Methods: participants, interventions, and outcomes

### Study setting {9}

Participants were recruited from the Center for Reproductive Medicine at Nanjing Drum Tower Hospital, China.

### Eligibility criteria {10}

***Inclusion criteria***
Women aged 38–42 years (inclusive) at the time of enrollmentBody mass index within the normal range (18.5–24.9 kg/m^2^)Undergoing controlled ovarian hyperstimulation with either a short-acting agonist protocol or an antagonist protocol;Scheduled for IVF/ICSI with PGT-ANumber of IVF/ICSI cycles ≤ 2

***Exclusion criteria***
Egg donation cycleKnown parental chromosomal abnormalitiesUterine disorders likely to impair implantation, including adenomyosis, uterine fibroids, uterine malformations, thin endometrium (< 7 mm), or endometriosis;History of recurrent implantation failure (≥ 3 failed embryo transfers with good-quality embryos)Severe systemic illness or uncontrolled endocrine/metabolic disease that may affect ovarian function (e.g., uncontrolled diabetes, thyroid dysfunction, or hyperprolactinemia)

Male partner eligibility is not restricted beyond a requirement for normal semen analysis; no additional exclusion criteria are applied to male partners. No restrictions are placed on study personnel or the participating center.

### Who will take informed consent? {26a}

Informed consent will be obtained by trained clinical research staff or the attending physician prior to any trial-related procedures. Participants will receive both written and verbal explanations of the study objectives, procedures, potential risks, and benefits. Sufficient time will be provided for questions and consideration. Written informed consent will be signed by each participant voluntarily.

### Additional consent provisions for collection and use of participant data and biological specimens {26b}

No additional consent will be required for the use of participant data beyond what is specified in the main consent form.

## Interventions

### Explanation for the choice of comparators {6b}

The standard control will consist of oocytes from the same individual that were cultured under routine IVF/ICSI laboratory conditions without MVA supplementation. This comparator represents the current standard of care in IVF/ICSI laboratory practice and allows for a direct evaluation of the effect of MVA treatment under otherwise identical conditions. By randomly allocating oocytes from the same patient into intervention and standard control groups, the design minimizes inter-individual variability and thereby enhances the internal validity of the study.

### Intervention description {11a}

A total of 150 PGT-A cycles will be included in the study. All retrieved COCs from each cycle will be randomly allocated into two parallel groups: the MVA supplementation group (intervention group) and the standard control group. Randomization will be performed at the level of sibling oocytes to minimize inter-individual variability.

#### Intervention group

COCs assigned to the intervention group will be incubated in fertilization medium supplemented with MVA metabolites at a concentration of 50 µM for 4 h prior to insemination. Following this exposure, all subsequent embryo culture procedures will be conducted according to standard IVF/ICSI protocols.

#### Standard control group

COCs in the standard control group will be cultured in standard fertilization medium without MVA supplementation for the same duration and under identical conditions as the intervention group. All laboratory procedures will be conducted under identical temperature, gas, and handling conditions to ensure consistency between groups.

#### Endometrial preparation

Endometrial preparation for frozen embryo transfer (FET) will be performed using hormone replacement therapy. From day 3 to day 16 of the menstrual cycle, patients will receive 4–6 mg/day of Femoston estradiol. Starting on cycle day 17, transvaginal ultrasound will be used to monitor ovulation status and evaluate endometrial thickness. Estradiol dosage will be adjusted according to individual endometrial response. Once the endometrium reaches a thickness of at least 8 mm, oral Femoston dydrogesterone combined with 60 mg of intramuscular progesterone will be administered daily for six consecutive days to complete luteal phase support.

#### Follow-up evaluation

Serum β-hCG levels will be measured 12 to 14 days following embryo transfer to confirm biochemical pregnancy.Approximately 30 days post-transfer, a transvaginal ultrasound will be performed to detect the presence of an intrauterine gestational sac with a visible fetal heartbeat. The flow chart of this study is shown in Fig. 1.

**Fig. 1 Fig1:**
[figure not shown]
Flow chart of the study

#### Criteria for discontinuing or modifying allocated interventions {11b}

Participants will be excluded from continued follow-up if any of the following conditions occur:Nonadherence to the prescribed treatment protocolUnplanned discontinuation of the embryo transfer procedureAdministration of additional medications that could potentially influence oocyte and embryo development during the study period.

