### Outcomes {12}

#### Primary outcome measure

The primary outcome measure is the euploid embryo rate: the ratio of the euploid embryos to the number of mature oocytes.

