#### Secondary outcome measures

Secondary outcome measures are the clinical pregnancy rate, miscarriage rate, and live birth rate.Clinical pregnancy rate: The ratio of the clinical pregnancy (intrauterine gestation sac with a fetal heart beat) number to the number of patients who received embryo transferMiscarriage rate: The ratio of the number of nonviable pregnancies before 28 weeks of gestation to the number of clinical pregnanciesLive birth rate: The ratio of the number of normal fetuses delivered after 28 weeks of gestation to the number of patients who received embryo transfer

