### Sample size {14}

Among women of AMA (38 ≤ age ≤ 42 years) undergoing treatment at this center, the current euploid blastocyst rate (defined as the number of euploid blastocysts per mature oocyte retrieved) is approximately 10%. This study is designed to increase this euploid rate to 17% with a significance level (α) of 0.05. To achieve this, each group is expected to include 371 mature oocytes, accounting for an estimated 10% dropout rate. This results in a final target of 408 mature oocytes per group. Given the average mature oocyte yield per cycle in women aged 38–42 years is approximately 5.45 oocytes, the study anticipates enrolling approximately 150 cycles in total.

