### Methods in analysis to handle protocol nonadherence and any statistical methods to handle missing data {20c}

Data will be analyzed following the ITT principle. Missing data will be analyzed. The imputation of missing values is not intended, although multiple imputations might be used within sensitivity analyses assuming data are missing at random.

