The primary endpoint, euploidy efficiency (euploid blastocysts per mature oocyte), was selected because it directly reflects meiotic fidelity and genomic stability. Secondary endpoints, including clinical pregnancy and live birth rates, were included to capture downstream clinical implications and to assess the potential translational impact of the intervention.

Several limitations should be acknowledged. First, it is open-labeled as the MVA-supplemented and standard media cannot be blinded; although this may introduce bias, the use of standardized procedures and an objective genomic endpoint minimizes subjectivity. Second, as a single-center trial, the generalizability of findings may be limited, though the intervention is simple and easily replicable. Third, the choice of euploidy efficiency as a surrogate endpoint enables feasibility with a smaller sample size but may not fully reflect clinical outcomes; therefore, pregnancy and live birth are included as secondary endpoints. Operational challenges include slow recruitment due to diminished ovarian reserve, strict standardization of intervention procedures, and potential attrition or missing data. These will be addressed through extended recruitment, detailed SOPs with staff training, and intention-to-treat analyses with retention strategies.

If effective, MVA supplementation could serve as a simple, low-cost upstream intervention that can be seamlessly integrated into standard IVF/ICSI protocols, potentially improving embryo usability and pregnancy outcomes in women of AMA. Scientifically, the trial will provide the first human evidence supporting the role of the MVA pathway in oocyte meiotic fidelity, thereby advancing understanding of reproductive aging mechanisms. Future research should investigate dose-response relationships, assess applicability in other populations such as younger women with diminished ovarian reserve, and conduct multicenter randomized trials powered for live birth outcomes to validate and extend these findings.

In summary, this trial evaluates a biologically grounded and operationally feasible intervention addressing the root cause of embryo aneuploidy in AMA. The results will inform both clinical practice and basic science, guiding next steps in optimizing fertility care for women of AMA.

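### Ending follow-up after nonadherence, a discontinued transfer or extra medication conflicts with the promised ITT analysis and adverse-event recording, mainly for the pregnancy and safety outcomes

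*Protocol article*

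**What the plan says.** The section on discontinuing or modifying interventions {11b} is worded as a requirement: "Participants will be excluded from continued follow-up if any of the following conditions occur". Its triggers are not following the treatment protocol, an unplanned stop to the transfer, and extra medication that might affect oocytes or embryos. The next section, on study suspension, adds loss of contact and incomplete follow-up as reasons for which participation may be suspended.

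Section {20c}, whose title covers protocol nonadherence as well as missing data, says: "Data will be analyzed following the ITT principle". On missing values it says: "The imputation of missing values is not intended, although multiple imputations might be used within sensitivity analyses assuming data are missing at random". The Discussion offers "intention-to-treat analyses with retention strategies" as part of its answer to attrition and missing data.

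Table 1 marks adverse events at every timepoint from T1 to T8 (1 month postpartum), and {22} has them recorded for the whole trial.

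On the unit of allocation, {11a} says: "Randomization will be performed at the level of sibling oocytes to minimize inter-individual variability". The primary outcome is "the ratio of the euploid embryos to the number of mature oocytes". Clinical pregnancy and live birth are expressed relative "to the number of patients who received embryo transfer", and miscarriage relative to clinical pregnancies.

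**The concern.** The article gives one event, nonadherence, two incompatible rules: stop following the woman ({11b}) and analyse her as allocated ({20c}). An analysis plan can define the ITT set, but it cannot restore outcomes that the protocol tells staff to stop collecting.

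The intervention is a single 4 h incubation before insemination, so a later event cannot undo the exposure. Removing a woman for such an event therefore selects on something that happened after allocation. Deciding whether a drug could affect embryo development takes judgement, and {17a} says that patients and researchers know the allocation. If the rule is followed as written, pregnancy, birth and adverse-event results could describe a subset chosen after randomization while carrying an ITT label.

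**Working it through.** The conflict is one of wording, so the first step sets the rule against the timeline. Arithmetic is used only to show the scale for the primary outcome.

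**1. Timing (Table 1).** Randomization is at T2 (in vitro fertilization), ploidy screening at T4, transfer at T5, and pregnancy and birth outcomes at T7 to T8. The primary outcome is marked at T4 and again at T5. The transfer trigger falls after randomization, and the other two can.

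**2. What each trigger removes.**

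| Trigger | Ploidy (T4) | Pregnancy, miscarriage, live birth | Adverse events to T8 |
|---|---|---|---|
| Nonadherence | Lost only if removal is before T4 | Lost for a woman who has had a transfer and is removed before the outcome is known | Lost from removal onward |
| Additional medication | As above | As above | As above |
| Discontinued transfer | Already read | Little added: without a transfer she is outside the pregnancy and live-birth denominators by definition | Lost from removal onward |

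**3. Effect on the main analysis.** Uncollected outcomes are missing. Multiple imputation is mentioned only as a possible sensitivity analysis under missing at random, so these women drop out of the main analysis of any outcome not yet recorded.

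**4. Effect on the primary comparison.** Each cycle's oocytes are split across two dishes ({16a}). Removing a woman before T4 removes oocytes from both arms, so the main loss is precision.

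The plan's own figure comes first. Inputs from {14}: 10% versus 17%, α 0.05, 10% dropout, 5.45 mature oocytes per cycle. {20a} makes the test two-sided. Power is not stated, so 80% is assumed.

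- n per group = (1.960 + 0.842)² × (0.10×0.90 + 0.17×0.83) / 0.07² = 370.2, rounded up to 371, as stated.
- 371 × 1.10 = 408.1, or 408, as stated.
- 2 × 408 / 5.45 = 149.7, or about 150 cycles, as stated.

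Power on the same basis (independent oocytes, pooled variance under the null):

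Φ{[0.07√n − 1.960√(2×0.135×0.865)] / √(0.10×0.90 + 0.17×0.83)}

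- n = 408: Φ{(1.414 − 0.947)/0.481} = 83.4%.
- n = 408 × 0.90 = 367: Φ{(1.341 − 0.947)/0.481} = 79.4%.
- n = 408 × 0.80 = 326 (20% loss, assumed): 74.5%.

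The 10% loss is already in the plan's allowance. No figure in {14} needs to change.

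**5. Effect on the secondary outcomes.** The article gives neither a frequency for these removals nor an expected pregnancy rate, so no bias can be computed.

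**The case against.** Four points on the other side have force.

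- The rule removes women from follow-up, not expressly from the analysis set. Data already collected can still be analysed as allocated. A reader might infer that an ITT analysis is impossible or that ploidy results will be missing. The text does not support that: ploidy is read before transfer, and a discontinued transfer cannot erase it.
- A discontinued transfer looks like the clearest source of bias, since it may itself reflect embryo quality. The secondary outcome definitions already leave out women without a transfer, so this trigger adds little to the pregnancy and live-birth comparisons.
- Loss of contact ends follow-up in any trial, and the suspension section says only that participation may be suspended. Listing it there does not by itself contradict ITT. It is better handled as missing data.
- A reader might try to size the effect as one woman over the number of cycles with a euploid embryo. With 5.45/2 = 2.725 oocytes per dish and independence, 150 × (1 − 0.90^2.725) ≈ 37 cycles have one of control origin and 150 × (1 − 0.83^2.725) ≈ 60 one of MVA origin. That suggests 1/37 = 2.7 or 1/60 = 1.7 points per woman. These are only upper bounds. Removing a woman changes numerator and denominator together, so the shift is p/(n−1) or (1−p)/(n−1): at an assumed p of 50%, 1.4 and 0.85 points. About 15 cycles (150 × 0.25 × 0.40) are counted in both groups. The 10% dropout in {14} concerns oocytes and cannot be read as a number of women removed.

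These points narrow the concern. They leave untouched the women who had a transfer and were then removed for nonadherence or medication: they belong in the stated denominators, yet their outcomes would go uncollected. The loss of adverse-event data also stands.

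**Conclusion.** The contradiction is real and should be corrected. As written, {11b} ends data collection on events that can follow randomization, against the ITT commitment in {20c} and the Discussion and against adverse-event recording to 1 month postpartum. The main exposure is in clinical pregnancy, miscarriage, live birth and adverse events, chiefly for women removed for nonadherence or medication after a transfer, in an open trial. The primary ploidy outcome is affected only by removals before T4, and then mainly through precision: power of about 83% falls to about 79% if 10% of oocytes are lost, assuming 80% design power and independent oocytes. The size of any bias in the secondary outcomes cannot be stated from the documents. Which clinical events should stop treatment is not judged here.

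**What to change.** Reconcile {11b}, the suspension criteria, the outcome definitions {12} and {20c} by separating the stopping of treatment from the stopping of data collection:

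- Record the three listed events as protocol deviations. Continue outcome and adverse-event follow-up unless the woman withdraws consent for use of her data.
- Analyse all mature oocytes in the dish to which they were allocated, and pregnancy outcomes by the allocated dish of the transferred embryo. A woman cannot be assigned to one dish, because her oocytes are split across both.
- Treat loss of contact as missing data.
- Keep any per-protocol analysis as sensitivity only.

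Trial status reports recruitment closed and the last biopsy done in January 2025, with last follow-up due in December 2025. New wording alone will not recover follow-up already stopped. Retrieve those outcomes from hospital records where consent allows, and report removals already made by reason and by the allocated dish of any transferred embryo.

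The cost is some extra data retrieval and, under {25}, ethics committee approval for any change that counts as an important amendment. The sample size does not change.

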#### Criteria for study suspension

Study participation may be suspended under the following circumstances:Voluntary request from the participant to discontinueSafety concerns, including adverse events (AEs) that the investigator deems clinically significant and related to the intervention or any AE that the participant considers intolerable, regardless of severityInability to obtain complete follow-up data or loss of contact with the participant

